#### **3.2.1.3 Safety Population**

The safety population includes all participants who completed the informed consent for the RCT component during the screening visit and received treatment. Safety analyses will be performed according to the participant's randomized treatment arm.

### **3.2.2 General Definitions**

#### **3.2.2.1 Index ED Visit**

The Index ED Visit is the first visit for participants and involves both screening and randomization.

#### **3.2.2.2 Study Day**

Study Day (or Day) is defined as the number of days post-index ED Visit with Study Day 0 defined as the date of randomization.

#### **3.2.2.3 7-day Follow-Up Visit**

The 7-day follow-up visit date is defined as the seventh study day. The actual visit can occur later, but information is only collected about events that occurred within 7 days of the index visit.

#### **3.2.2.4 30-day Follow-Up Visit**

The 30-day follow-up visit date is defined as the 30th study day. The actual visit can occur later, but information is only collected about events that occurred within 30 days of the index visit.

#### **3.2.2.5 Treatment Emergence**

Treatment emergence is used to determine the temporal relationship of an adverse event to study treatment administration. The window for treatment emergence begins on the day of first dose and ends 30 days later (first dose date to first dose date + 30 days, inclusive). The first dose date for XR-BUP will be the date the injection was administered in the ED. The first dose date for SL-BUP will be the date of enrollment provided the medication was administered in the ED or prescribed for home induction.

#### **3.2.2.6 Adverse Event**

An adverse event (AE) is any untoward medical occurrence in humans, whether or not considered study medication/intervention related which occurs during the conduct of a clinical trial. Any change

from baseline in clinical status, ECGs, lab results, x-rays, physical examinations, etc., that is considered clinically significant by the site medical clinician are considered AEs.

### **3.2.2.7 Serious Adverse Event**

An adverse event is considered “serious” if, in the view of either the site medical clinician or sponsor, it:

- Results in death: A death occurring during the study or which comes to the attention of the study staff during the protocol-defined follow-up period, whether or not considered caused by the study [medication/intervention], must be reported.
- Is life-threatening: Life-threatening means that the study participant was, in the opinion of the medical clinician or sponsor, at immediate risk of death from the reaction as it occurred and required immediate intervention.
- Requires inpatient hospitalization or prolongation of existing hospitalization.
- Results in persistent or significant incapacity or substantial disruption of the ability to conduct normal life functions.
- Is a congenital abnormality or birth defect.
- Is an important medical event that may not result in one of the above outcomes but may jeopardize the health of the study participant or require medical or surgical intervention to prevent one of the outcomes listed in the above definition of serious event.

## **3.3 Table, Figures and Listings Conventions**

For the Ancillary component, all tables, listings, and figures will be presented overall and by site unless noted otherwise. Tables will include a total column or row. For the RCT component, all tables, listings, and figures will either be presented by treatment arm or by site, and in either case, tables will include a total column or row. The descriptive text in the SAP, or the name of the table, listing, or figure, will indicate whether it is by treatment arm or site. Sites in the Ancillary component that did not enroll or randomize any participants will only be included in presentations that have screening information.

Descriptive summaries for continuous variables will include the number of non-missing values, mean, standard deviation, minimum, 25th percentile, median, 75th percentile, and maximum. In general, the mean, median, and any percentiles presented will be to one greater decimal (precision) than how the variable was measured. For example, COWS is measured as an integer so the mean and median should be rounded to one decimal place. Standard deviation will be rounded to two greater decimals. Minimum and maximum (and any other statistic that is an element of the data) will be presented in the same precision as captured. In cases of inconsistent precision within a variable, the mean and median will generally be rounded to one decimal place, the standard deviation to two, and minimum and maximum to one decimal place.

Categorical variables will be summarized by frequencies and percentages. Percentages will generally be rounded to one decimal.

## **4.0 PARTICIPANT ENROLLMENT, DISPOSITION, AND VISIT ATTENDANCE**

### **4.1 Ancillary Component**

#### **4.1.1 Participant Enrollment**

The number of participants screened and the corresponding reasons for ineligibility on screening will be summarized by site.

The trajectory of actual enrollments versus the expected number of enrollments (according to the first date of enrollment and under the assumption that 3.12 participants are expected to be

enrolled per month per site) along with the proposed number of enrollments will be graphed by site and overall. Proposed versus actual enrollments will be summarized by site in a tabular fashion. These presentations will be generated for the Primary Ancillary Analysis and Full Ancillary Analysis populations.

#### **4.1.2 Participant Disposition**

Participants are defined as study completers if the Day 7 Visit is completed as indicated on the Study Completion (STC) form, and they are considered early study terminations if this visit is not completed. Participant disposition will be summarized by site for the number of participants completing the study, the number of participants terminating early from the study, and the reasons for early study termination.

The participant flow diagram will be generated

#### **4.1.3 Visit Attendance**

The number and percent of participants who completed the Day 7 visit as expected will be summarized by site for the Primary Ancillary Analysis and Full Ancillary Analysis populations.

### **4.2 RCT Component**

#### **4.2.1 Participant Enrollment**

The number of participants screened and the corresponding reasons for ineligibility on screening will be summarized by site.

The trajectory of actual randomizations versus the expected number of randomizations (according to the first date of randomization and under the assumption that 7 participants are expected to be randomized per month per site) along with the proposed number of randomizations will be graphed by site and overall. Proposed versus actual randomizations will be summarized by site in a tabular fashion. These presentations will be generated for the Full Ancillary Analysis population.

The distribution of treatment assignments by site and insurance status used for randomization will be presented by treatment arm for the ITT population.

#### **4.2.2 Participant Disposition**

Participants are defined as study completers if the Day 30 Visit is completed as indicated on the Study Completion (STC) form, and they are considered early study terminations if this visit is not completed. Participant disposition will be summarized by site for the number of participants completing the study, the number of participants terminating early from the study, and the reasons for early study termination. This table will also be presented by treatment arm.

#### **4.2.3 Visit Attendance**

The number and percent of participants who completed the Day 7 and Day 30 visits as expected will be summarized by treatment arm.

## **5.0 ANALYSIS OF PARTICIPANT BASELINE CHARACTERISTICS**

### **5.1 Ancillary Component**

Baseline demographics and characteristics including sex, age (as continuous and categorical), ethnicity, race, education completed, marital status, employment, housing status, baseline COWS score (as continuous and categorical (0-3, 4-7)), insurance status, baseline UDS results, days since last self-reported opioid use at baseline, and most severe route of most recent self-reported

opioid use at baseline will be summarized overall and by site for the Primary Ancillary Analysis and Full Ancillary Analysis populations.

## **5.2 RCT Component**

Baseline demographics and characteristics including sex, age (as continuous and categorical), ethnicity, race, education completed, marital status, employment, housing status, baseline COWS score (as continuous and categorical: 4-7,  $\geq 8$ ), insurance status, baseline UDS results, number of days since last self-reported opioid use at baseline, number of days of opioid use in the week prior to randomization, and most severe route of most recent self-reported opioid use at baseline will be summarized by treatment arm for the ITT population.

In a small number of cases, insurance status reported at randomization (ER0099RC.E99RINSR) may differ from actual insurance status. The baseline table will summarize the actual insurance status (P99.P9INSURN).

## **6.0 STUDY MEDICATION ADHERENCE**

### **6.1 Ancillary Component**

#### **6.1.1 Treatment Exposure**

The number and percent of participants who received the XR-BUP injection will be summarized by site.

### **6.2 RCT Component**

#### **6.2.1 Treatment Exposure**

The number and percent of participants exposed to treatment will be summarized by treatment arm.

- Participants randomized to XR-BUP will be counted as exposed if they received the injection (ENROLL.TRTRUE = XR-BUP and INJ.ININJADM = 1).
- Participants randomized to SL-BUP will be counted as exposed if they were dosed in the emergency room or sent home with an induction dose (ENROLL.TRTRUE = SL-BUP and (SLB.SLSLBADM = 1 or SLB.SLNSLBSP = 02)).

## **7.0 EFFICACY ANALYSIS**

### **7.1 Ancillary Component**

#### **7.1.1 Definition of Primary Outcome Measures**

There are three primary outcome measures for the Ancillary component. The percent of Primary Ancillary Analysis participants that experience each of the following will be calculated:

- 1. Participant experienced a 5 or greater increase in COWS score within 4 hours of XR-BUP injection.**
  - A participant's COWS score is measured on the COW eCRF at baseline, 30, 60, 90, 120, 150, 180, 210, and 240 minutes post injection. A participant experiences an increase of 5 or greater if the COWS score at any of the post-baseline measurements listed is 5 or greater than the COWS score at baseline.
  - In order for this outcome to be evaluable (i.e., non-missing), a participant must have one pre-injection (baseline) COWS score and at least two post-injection COWS scores, one of which is collected within the last hour of the 4-hour period after the

injection. If a participant only has one pre-injection (baseline) COWS score and one post-injection COWS score which indicate an increase of 5 or greater from baseline, this outcome is considered evaluable (as having met the criterion for this outcome).

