## 12.5 Sample Size Justification for Ancillary Study

The objective of this pilot study is to examine 4-h changes in opioid withdrawal signs and symptoms among patients who have a COWS score  $<8$  and receive ED-initiated XR-BUP. We will estimate the proportion of participants that: a) experience a 5 or more point increase in COWS score in 4-h following XR-BUP administration; b) transition to moderate withdrawal (COWS score of 13-24) during 4-h after XR-BUP administration; and c) experience clinician determined precipitated withdrawal within 1-h of XR-BUP administration. A sample size of 75 was determined to be sufficient to estimate these proportions with reasonable precision. Table 5 below shows the precision (actual 95% Exact Clopper Pearson confidence interval width) for different proportions. For instance, if the proportion is 0.01 (or 1%) the 95% confidence interval will have a width (i.e., difference between upper and lower 95% confidence bounds) of .066 (or ~7%). Point estimates of 5%, 10%, and 20% will have widths of 11%, 15% and 19% respectively. A sample size of 100 will decrease these widths further.

12.5.1 Table 5: Two-Sided Exact (Clopper Pearson) 95% Confidence Intervals Width for Different Proportions

| Proportion      | 0.01  | 0.05  | 0.1   | 0.15  | 0.2   | 0.25  | 0.3   |
|-----------------|-------|-------|-------|-------|-------|-------|-------|
| Actual CI Width | 0.066 | 0.113 | 0.148 | 0.173 | 0.192 | 0.206 | 0.217 |

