## **3. Participant experienced a precipitated withdrawal within 1 hour of XR-BUP injection**

- Potential precipitated withdrawal events are adjudicated by study consultants and captured on the PWD eCRF as 'Yes' or 'No' at 240 minutes after the XR-BUP injection. If the time listed for this precipitated withdrawal is within 1 hour of the time of XR-BUP injection (including exactly 1 hour), the participant is considered to have experienced this outcome.
- In order for this outcome to be evaluable (i.e., non-missing), the PWD eCRF must be completed with a time of precipitated withdrawal provided one occurred.

For all three outcome measures, if the outcome measure is not evaluable (i.e., missing), the worst-case scenario will be imputed for that outcome measure where the participant is assumed to have experienced the outcome measure.

The *a priori* conditions on these outcomes in the Primary Ancillary Analysis population to inform expanding enrollment in the RCT component are:

- <20% of participants will experience a 5 or greater increase in COWS score within 4 hours of injection
- <10% of participants will transition to moderate withdrawal (COWS score 13 to 24, inclusive) within 4 hours of injection
- <10% of participants will experience precipitated withdrawal within 1 hour of injection

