### **7.1.2 Analysis of the Primary Outcome Measures**

Each of the three primary outcome measures will have the percent (as proportions) of the Primary Ancillary Analysis population experiencing the outcome estimated. A 95% confidence interval, calculated by the Exact Clopper-Pearson method, will also be provided for each outcome measure. The following is template SAS code to generate the proportions and confidence intervals:

```
proc freq data = dat;  
    table outcome / binomial(cl=exact level='1') alpha=0.05;  
run;
```

where `dat` is the name of the dataset with one row per participant and `outcome` is the name of any of the outcomes above coded as '0' for not experiencing and '1' for experiencing the outcome.

If the upper limits of the above confidence intervals are less than the *a priori* condition on the outcome (Section 7.1.1) in the Primary Ancillary Analysis population, the *a priori* condition is considered achieved.

A listing will be provided of participants that experienced at least one of the outcomes to present which participants experienced any combination of the primary outcome measures.

The summary table of primary outcomes is presented overall and not by site.

The availability of data to compute the primary outcomes will be summarized by site.

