| Total                                                                                  |                 |                            |                                      |                      |                                                 |                      |

 Three COWS assessments are required: pre-injection COWS, and two post-injection COWS, one of which is within the last hour.

 The denominator is the number of participants enrolled.

| Table 13: Summary of Primary Outcome Analysis (Primary Ancillary Analysis Population) |                                                                                                      |           |                                      |
|---------------------------------------------------------------------------------------|------------------------------------------------------------------------------------------------------|-----------|--------------------------------------|
| Number Enrolled                                                                       | Primary Outcome Measure                                                                              | N (%)     | 95% Confidence Interval  |
| N                                                                                     | Participant experienced a 5 or greater increase in COWS score within 4 hours of the XR-BUP injection | N (xx.x%) | xx.xx% - xx.xx%                      |
|                                                                                       | Participant transitioned to moderate withdrawal within 4 hours of the XR-BUP injection               | N (xx.x%) | xx.xx% - xx.xx%                      |
|                                                                                       | Participant experienced a precipitated withdrawal within 1 hour of the XR-BUP injection              | N (xx.x%) | xx.xx% - xx.xx%                      |

Missing COWS scores or precipitated withdrawals are imputed as having experienced the event.

 Calculated using the Exact Clopper-Pearson method.

Table 14: Summary of Primary Outcome Analysis (Full Ancillary Analysis Population)

- repeat Table 13 for Full Ancillary Analysis population

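### Ancillary outcomes 1 and 2 count a participant with no COWS score in the first three hours as a confirmed non-event, and no sensitivity analysis covers this case

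*Combined protocol and SAP*

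**What the plan says.** SAP 7.1.1 schedules COWS at baseline and at eight times after injection, every 30 minutes from 30 to 240. Outcome 1 is met if any post-injection score is at least 5 points above baseline. Outcome 2 is met if any post-injection score is 13 or more. Both are therefore outcomes of the form *ever within 4 hours*.

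For both, the participant is evaluable with a baseline score and "at least two post-injection COWS scores, one of which is collected within the last hour of the 4-hour period". A single post-injection score is enough if it shows the event. The footnote to Table 12 (primary outcome availability) repeats the standard: "Three COWS assessments are required: pre-injection COWS, and two post-injection COWS, one of which is within the last hour".

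If an outcome is not evaluable, "the worst-case scenario will be imputed for that outcome measure", so the participant counts as having had the event. SAP 7.1.4 adds complete-case and best-case analyses. These are optional if any outcome is missing, and are promised only when more than 5% are missing.

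The a priori conditions are "<20% of participants will experience a 5 or greater increase in COWS score within 4 hours of injection" and "<10% of participants will transition to moderate withdrawal (COWS score 13 to 24, inclusive) within 4 hours of injection". SAP 7.1.2 judges them on the upper limit of the exact two-sided 95% interval, as does Protocol 12.6.6.

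**The concern.** A statement that something never happened in four hours needs observation across the four hours. The rule secures the end of the period but not the beginning. A participant first scored at 210 minutes enters the analysis as fully observed and event-free, with the same standing as one scored at all eight checks.

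The safeguard for incomplete data does not reach this participant. Worst-case imputation, the two sensitivity analyses and the availability count in Table 12 all depend on the outcome being classed as missing, and here it is not.

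At stake is how well the low-COWS event rates are supported. These criteria informed the decision to open the RCT to patients with COWS below 8. The early period also matters clinically in this component: the third primary outcome concerns the first hour.

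**Working it through.** **1. How three event-free participants are classified under SAP 7.1.1.**

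| Scores after injection, all flat | Score in last hour? | Evaluable? | Counted as |
|---|---|---|---|
| All eight checks | yes | yes | non-event |
| 30, 60, 90, 120, 150 only | no | no | event (imputed) |
| 210, 240 only | yes | yes | non-event |

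The second participant has five scores and the third has two, yet only the second is handled conservatively. A rise that has resolved before 210 minutes cannot be seen in the third. With checks every 30 minutes, any rise that lasts 30 minutes or more and falls within the schedule would be seen in the first.

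**2. Direction.** Any observed event counts, however few the scores. Sparse scoring can therefore turn a true event into a non-event but never the reverse, so this rule taken alone can only lower the event rate.

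**3. How many schedules the rule permits.** Count subsets of the eight times with at least two scores, one in the last hour. The SAP does not say whether 180 minutes lies in the last hour, so both readings are shown.

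- If 180 counts: 7 × 2⁵ − 3 = 221 permitted patterns. Of these, 7 × 2³ − 3 = 53 have no score at 30 or 60 minutes, and 7 × 2 − 3 = 11 have none up to 120 minutes.
- If 180 does not count: 3 × 2⁶ − 2 = 190, of which 3 × 2⁴ − 2 = 46 and 3 × 2² − 2 = 10.

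The pair 210 and 240 qualifies under both. These are counts of permitted patterns, not of participants.

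**4. The plan's own figures.** Inputs are n = 75 (Protocol 12.5: "A sample size of 75 was determined to be sufficient to estimate these proportions with reasonable precision") and the method of SAP 7.1.2: "A 95% confidence interval, calculated by the Exact Clopper-Pearson method, will also be provided for each outcome measure". For x events, the lower limit is the 0.025 quantile of Beta(x, 76 − x) and the upper limit is the 0.975 quantile of Beta(x + 1, 75 − x).

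| Proportion | 0.01 | 0.05 | 0.10 | 0.15 | 0.20 | 0.25 | 0.30 |
|---|---|---|---|---|---|---|---|
| Width stated (SAP 10.1) | 0.066 | 0.113 | 0.148 | 0.173 | 0.192 | 0.206 | 0.217 |
| Width recomputed | 0.0664 | 0.1134 | 0.1485 | 0.1732 | 0.1918 | 0.2062 | 0.2173 |

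All agree to within 0.001.

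**5. Where the criteria turn.** The decision sentence in SAP 7.1.2 begins "If the upper limits of the above confidence intervals are less than the" stated condition. Applying the upper-limit formula:

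| Outcome (threshold) | Last passing count | Upper limit | First failing count | Upper limit |
|---|---|---|---|---|
| 1 (20%) | 8/75 = 10.7% | 19.94% | 9/75 = 12.0% | 21.56% |
| 2 (10%) | 2/75 = 2.7% | 9.30% | 3/75 = 4.0% | 11.25% |

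With x observed events, reclassifying 9 − x participants (outcome 1) or 3 − x (outcome 2) would reverse a pass. That is one participant at the boundary, and nine or three starting from zero.

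**6. Why the 5% trigger does not help.** Late-only participants are not counted as missing, so they do not contribute to the trigger. Even if they did, three of about 100 in the Full Ancillary population is 3%, below the trigger, although three is enough to fail outcome 2.

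**The case against.** The strongest reply is that the pattern may hardly occur. Scores are due about every 30 minutes under in-person observation (Protocol 9.1.2, Table 4, 14.4). Being scored only at 210 and 240 minutes means six consecutive missed checks in a patient who is still present. Nothing in the documents suggests that this happened. This stands, and it limits the point to one of unknown size.

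Early harm is also recorded elsewhere. Outcome 3 captures adjudicated precipitated withdrawal within one hour on its own form, with its own worst-case rule. Post-injection medications are listed with times (SAP 8.1.5), and COWS change is plotted per participant (SAP 8.1.2). A reader might infer that early withdrawal is lost from the study; the documents do not support that. But none of these sources changes how outcomes 1 and 2 are classified.

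Other rules push the other way. The Primary Ancillary population is defined by consent and does not require injection (SAP 3.1.1.2). An uninjected participant is therefore not evaluable and is imputed as an event, as is one who leaves early. A reader might infer that the ancillary event rates are biased downwards overall; the net direction cannot be established from the documents.

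Finally, a demanding coverage rule would overcorrect. If both the 30- and 60-minute scores were compulsory, a participant flat at seven checks who missed only the first would be imputed as an event, and three such participants would fail outcome 2 with no observed event. This also stands, and it shapes the fix.

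**Conclusion.** The gap is real for outcomes 1 and 2 and for the Table 12 availability count. An event-free classification can rest on two late scores, while better-observed participants without a last-hour score are imputed as events. The effect of this specific rule is towards a lower event rate.

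Its size cannot be given. It depends on how many participants had sparse early schedules and on when rises start and end, and the documents report none of these. What can be said is that one reclassified participant would reverse a criterion if the count sits at 8 (outcome 1) or 2 (outcome 2).

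A reader might go further and infer that the expansion of RCT eligibility is unsound. The documents do not support that. Meeting the criteria required approval by the steering committee and DSMB, and missing them led to DSMB review (Protocol 12.6.6). The DSMB did review the first 75 participants and agreed to COWS 4 to 7 (Protocol 8.10). The point concerns how firmly the reported rates are supported, and it can be checked with data already collected.

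**What to change.** Keep the primary definition in SAP 7.1.1. The DSMB has reviewed results for the first 75 participants, and a primary outcome should not be redefined after that.

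Add to SAP 7.1.4 a labelled sensitivity analysis for outcomes 1 and 2, to be presented whatever the proportion missing:

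- An event-free participant with no COWS score in the first hour (neither 30 nor 60 minutes), or with a long run of consecutive missed checks, is treated as not evaluable and scored worst case. Three or more missed checks is a reasonable example, since it leaves at least 4 × 30 = 120 minutes between neighbouring scores.
- Any observed event still counts, and a single missed check changes nothing.

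State whether 180 minutes lies in the last hour. Add to Table 12 the number of post-injection COWS scores per participant and the number of participants with no first-hour score. The Missed Post-injection Assessments form, already in the list of eCRFs, can support this.

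The cost is one more table and a few added rows, with no new data. The sensitivity rates may be slightly less favourable than the primary ones. If no participant meets the rule, the analysis will show that the concern has no practical effect.
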